***3.0*** **Any other comments that you think are relevant to this discussion but I have not mentioned**

## Annex 3 interview guide for KIIs for sub study one

***2.1 Prevention and Promotional activities during ANC***-what are the activities that you routinely conduct during antenatal care at the health facility; (here we probe for history taking, physical examinations, laboratory examinations, Ferrous, Albendazole prophylaxis, health education, assessment for referral,

**What vital health education messages** are provided at this stage of pregnancy in addition to other curative services like Tetanus vaccination, test for Syphilis and HIV; explore for any birth preparation messages (clothing, finances, the relative who will be assisting her during labour, in case of emergency delivery); approaches for clean delivery, use of sterile instruments, tying of the cord, application of substance to the cord, ensuring warmth for the baby, initiation of breast feeding, any specific messages regarding warmth, breast feeding and hygiene, pre-lacteal feeding; what advice is given to the mother about care for the mother and the new born baby (in terms of feeding, hygiene, warmth and care for the cord

***2.5 Their frustration with this process***-What are/is their frustration with the process of providing the comprehensive ANC package - curative as well as preventive and promotional healthcare services to pregnant mothers and newborn babies; explore for the workload, the time needed to provide the necessary information; the challenges with late arrivals of the mothers and the newborns

***2.6 What they think about VHT performing some of these functions***-What is their opinion about sharing the burden of work with VHTs; what can the VHTs do to bridge this gap; which aspects of care do they think CHWs can do better; which aspects of care are the PHC workers are more comfortable with; how can the two separate roles be harmonised;

***2.7 What relationship they advocate for***-What kind of relationship would they want to see between the formal healthcare system and the CHW/VHTs; what they think about separation of roles between PHC workers and the VHTs; would they encourage consultations from VHT members, or referrals from the VHT; how would they like these referral system to function

***2.8 Possible linkage with formal healthcare system***-how do they think linkages can be created; what activities can the formal healthcare system perform together with the VHTs; how can the functions of the VHTs be monitored; how can the VHTs be supported to function better; how can VHTs enhance the uptake and utilisation of the services organised at the formal health system to reduce on the delays at home

***2.9 How telecommunication can enhance this linkage***-Is there any role for telecommunications in enhancing the linkage between the formal healthcare system and the VHTs; can the telephone system be used for consultations with the first-line health services; is this likely to work; can mobile phones be used to provide reminders to pregnant women through the VHTs; what are the challenges this intervention is likely to encounter; are they (the health workers) ready to be consulted by phone

## Annex 4 Focal persons for the Key-Informant Interviews for sub study one

| **S/N** | **Officer to be Interviewed** | **Number** |
| --- | --- | --- |
| 1 | District Health Officer | 2 |
| 2 | Medical Superintendent | 2 |
| 3 | Officer in charge of the Community Health Department | 2 |
| 4 | Principal Nursing Officer | 2 |
| 5 | Head of Unit Maternity | 2 |
| 6 | Head of Unit Antenatal Unit of hospital | 2 |
| 7 | Midwives Based at the health centres II, III, IV | 8 |
|  | **TOTAL** | **20** |

## Annex 5 Sampling procedure for sub study two

Districts Masindi & Kiryandongo

Parishes (**21**)

**3** Villages per Parish

Lactating women with babies up to two months or sixty days at the time of the study **(823)**; regardless of parity and where delivery took place for semi-structured interview

Purposively identify **6** TBAs from any of the parishes and **6** elderly home caregiver from any of the parishes selected for KII interview;

Identify **30** lactating mothers from each of the following age groups: 10-13 years; 14-16 yrs; 17-19 yrs and 20 years and above for In-Depth Interviews

## Annex 6: data collection guide for Structured Interview for lactating women sub study two

Data collection (adapted from ([Bagui A, Williams E et al. 2007](#_ENREF_3); [Bazzano A, Kirkwood B et al. 2008](#_ENREF_9); [Darmstadt G, Mohamed H et al. 2008](#_ENREF_24); [Kesterton and Cleland 2009](#_ENREF_47))

**Optimization of individual prenatal education offered to pregnant women in Masindi and Kiryandongo district, Western Uganda: A community Intervention trial**

Data collection tool for lactating women;

**A: Socio-demographic characteristics**

1. Code number..........................................................................................
2. Name of household Head........................................................................
3. Age of Respondent in completed years (lactating woman)....................
4. Parity of respondent 1, 2, 3, 4, 5, over 5
5. Highest education level attained:
6. Non
7. Primary;
8. Secondary;
9. High school;
10. Tertiary;
11. Marital status:
12. Married
13. Single
14. Separated
15. Divorced
16. Widowed
17. What do you do for a living:
18. Nothing
19. Housewife
20. Farming/gardening
21. Selling in the market/petty trade
22. Business woman
23. Salaried
24. Did you attend any ANC during the last pregnancy:
25. Yes, 2. No
26. Number of ANC visits made with the last pregnancy:
27. 0,
28. 1,
29. 2,
30. 3,
31. 4
32. More than 4
33. Where did this last delivery take place:

**1)** Home;

**2)** Health facility;

**3)** On the way to health Facility

1. How old is the baby now? Age in completed weeks
2. 0-1 week **2)** 2-4 weeks **3)** 5-8 weeks **4)** 9-13 weeks
3. Number of living children: 1, 2, 3, 4, 5, 6, more than 6
4. Number of deceased children: 0,1, 2, 3, 4, 5, 6, more than 6

(*if deceased babies is* ***0*** *then skip to section* ***B***)

1. At what ages did the deceased children die?

**a) First death,**

1) Died as a still birth

2) Within 24 hours

3) After 24 hours but within 72 hours

4) After 72 hours but within 7 days

5) After 7 days but within 28 day

6) After 28 days

**b) Second death,**

**1**) Died as a still birth

**2**) Within 24 hours

**3**) After 24 hours but within 72 hours

**4**) After 72 hours but within 7 days

**5**) After 7 days but within 28 day

**6**) After 28 Days

**c) Third death,**

**1**) Died as a still birth

**2**) Within 24 hours

**3**) After 24 hours but within 72 hours

**4**) After 72 hours but within 7 days

**5**) After 7 days but within 28 day

**6**) After 28 Days

13. Indicate where the deceased babies were were born from:

**1)** At home

**2)** At health facility

**3)** On the way to Health facility

**B: Data on the last pregnancy**

1. During your last pregnancy is there any food that was forbidden for you to eat?

1=Yes

2=No

1. If YES why?

1) will make the baby grow too big

2) will cause the baby to come out;

3) other, Specify...................

1. During this pregnancy were you advised not to take part in certain activities?

1=Yes

2=No

1. If YES, please *(circle all that apply)*:

1) Not going to the well to fetch water

2) Not using a pit latrine

3) Not engaging in sexual intercourse

4) Other, please Specify...................

1. Did you make any preparation for this delivery?

1=Yes

2=No

1. If YES, what specific preparations did you make? *(Circle all that apply)*

**1**) Secured warm dresses and other items for the baby like basin,

**2**) mama kit, mackintosh,

**3**) saved some money,

**4**) decided where to deliver from,

**5**) selected a caretaker for the remaining children while I am away ,

**6**) other, please specify

**C: Information on Delivery**

1. Mode of delivery of the current baby:

**1**) Spontaneous Vaginal delivery;

**2**) C/S

**3**) vacuum;

4) Forceps

1. Place of delivery:

**1)** health centre,

**2)** hospital

**3)** home

**4**) on the way to Health Facility

**5)** At the TBAs home

1. Who attended to you during delivery

**1**) By trained health worker

**2**) A close relative

**3**) By TBA

**4)** Unattended to

1. Timing of labour-in your view was this labour:

**1)** Normal

**2)** Longer than usual

**3)** Too long

**4)** Too short

**5)** No idea

1. Did you develop any intra-partum complication: *(Circle all that apply)*
2. too long labour
3. bleeding
4. swelling of the feet
5. convulsions
6. ruptured uterus
7. obstructed labour
8. non

**D. Clean delivery**

**T**

1 What instrument was used for cutting the cord?

1. New razorblade
2. Sterilised instrument
3. Used/old razor blade
4. A knife
5. Other sharp objects used in the household
6. What instrument was used to tie the cord?
7. Clean thread was used
8. Application of spirit/alcohol
9. Thread from household cloth
10. Pieces of used cloth
11. What substance was applied on the cord?
12. Application of powder on the stump
13. Application of animal waste
14. Application of soot powder
15. Salt water
16. Herbal medicines
17. Nothing

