# Annex 15: SOPs: Standard Operating Procedure and intervention packages

### i) Standard operating procedure and intervention package for educational intervention during ANC

**(**[**Bhutta Z, Sajid S et al. 2011**](#_ENREF_10)**)**

When the pregnant women enter the clinic room

1. Identify pregnant women with all of the following conditions:
2. First visit of the current pregnancy,
3. Not more than 28 weeks of gestation
4. Administer the consent form
5. If she consents then open a file for her
6. Request for her ANC card
7. Enter all personal details available on the ANC card in to the file
8. Record any telephone contacts that you can use to access her in future

name, age, ethnicity, parity, LNMP, EDD, gestation age of the first visit, history of previous pregnancy outcome of the previous pregnancy (baby – alive or dead, mode of delivery), distance from the health facility, marital status, history of previous ANC attendance-Number of attendance, delivery (home, health facility, TBA etc).

Note the date for the next appointment, (all this information will be used to tailor the discussions)

-if she consistently attended all the expected milestones-then you find out what her motivation was to do so, and whether she plans to do the same for the current pregnancy;

- If not consistent-discuss the reasons for inconsistencies and help her to find a solution,

- diet during pregnancy-find out what foods are readily consumed and what she can easily afford, what foods could be prohibited during pregnancy (caution about antagonising cultures-you can find another acceptable alternative source of the food value) and discuss the importance for balances in diet, fruits, green vegetables, proteins and carbohydrates,

- Discuss work related activities-how much she does and who helps her with the routine household and garden chores.

- Discuss importance of ANC even when she has been attending consistently, the advantages of delivering in the health facility even when she has been delivering at the health facility,

- Birth preparation-clean clothes for the newborn (emphasis that clean does not mean new!-even old rages can be patched together washed clean, clean environment for the newborn,

- caring for the cord, dangers of applying substances to the cord,

- Pre-lacteal feeds-and its disadvantages-explain how breast milk eventually comes and the usefulness of colostrum.

- Discuss bathing of the new baby how soon and how to delay (delay up to 24 hours),

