- Immunisation of the child, polio 0, BCG etc.

- Recognition of a sick child-hot to touch, refusing to feed, crying unusually,

All these information should be derived from discussions with the pregnant woman-not as a set of instructions to be strictly followed-compromises should be made at every stage-all that is agreed upon should be detailed down in the file. The counsellor should moderate the discussions, if the pregnant woman has come with a partner or a caretaker; both of them should be involved in the discussions even if the care taker is not pregnant-if there is a caretaker present then this should be recorded and state the relationship between them.

Tick the areas that were discussed, mark with a cross what you did not discuss with her, note down important decisions that you have agreed upon with the participant-you will use this as a reference point in subsequent meetings and discussions

Ensure that the discussion does not exceed 30 minutes unless there is expressed interest from the participant to continue. And this expression should be noted down in the file.

For subsequent visits indicate appointment dates and actual revisit dates

Later on follow-up for delivery and record where she has delivered from

Assess for the different practices outlined annex 6 will be used to assess the following outcomes

Place of delivery, Cutting of the cord, care for the cord, initiation of breast feeding, provision of pre-lacteal feeds, in case of illness how it was recognised, what action was taken, how soon was the care seeking from onset of disease or when the decision was made that the child was unwell, what facility did she take the child, outcome, at the periphery of assessment the researcher will want to know whether the child is still alive just at one month.

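### The cord questions in Annex 6 list spirit/alcohol as something that ties the cord and not as something applied to it, so clean thread plus spirit cannot be recorded correctly with one answer per item

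*Protocol*

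**What the plan says.** Annex 6 section D asks "What instrument was used to tie the cord" and gives four answers, in this order: "Clean thread was used", "Application of spirit/alcohol", "Thread from household cloth", and pieces of used cloth. It then asks "What substance was applied on the cord" and gives six answers: powder, animal waste, soot, salt water, herbal medicines, and nothing. Spirit or alcohol is not among the six.

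Neither question has an open answer, although section B of the same annex uses one ("Other, please Specify"). Neither tells the interviewer that several answers may be circled, although items in sections B, C and H do.

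The form serves two purposes. It is the structured interview for sub-study two (section 4.3.6). The procedure for the trial's educational package (Annex 15, SOP i) also points to it for outcome assessment: "Assess for the different practices outlined annex 6 will be used to assess the following outcomes". Cutting of the cord and care for the cord follow as separate entries in that list. Section 4.4.7 names cord care as one of four newborn care practices, and section 4.4.1 makes newborn homecare one of four primary outcomes.

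**The concern.** Spirit is a substance, not a tie, so one answer sits under the wrong question. The two questions are meant to capture different facts: whether the tie was clean, and whether anything was put on the cord. The misplaced answer makes them compete whenever spirit was used.

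The second fact is also one that the intervention tries to change, since the package covers "caring for the cord, dangers of applying substances to the cord". If spirit users can be entered as having applied nothing, the form blurs that behaviour. What was never recorded cannot be restored by a later analysis plan, so the point belongs to the form and has to be settled before data collection.

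**Working it through.** No figure in the protocol is at issue, so the check is to set the two answer lists side by side and see what each true situation produces.

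**Is the misplacement real?** The run-on numbering of the answers comes from text extraction and is ignored here. The position of the answer is harder to explain that way, because it stands between two thread answers. Its wording, which begins with application, matches the first three answers of the substance question and none of the tie answers. It reads as an answer placed under the wrong question.

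**How many records are possible?** With one answer per question there are 4 × 6 = 24 pairs. None of them is clean thread with spirit applied.

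**What is recorded?** Take the case where nothing else was applied and the interviewer enters nothing at the substance question. A blank or a wrong substance is also possible.

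| True situation | Tie answer chosen | Substance answer | What is lost |
|---|---|---|---|
| Clean thread, nothing applied | Clean thread | Nothing | Nothing lost |
| Clean thread, spirit applied | Clean thread | Nothing | Spirit use |
| Clean thread, spirit applied | Spirit/alcohol | Nothing | Clean tie |
| Used cloth, spirit applied | Spirit/alcohol | Nothing | Unclean tie |
| Used cloth, spirit applied | Used cloth | Nothing | Spirit use |

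Rows 1 and 2 give the same record, as do rows 3 and 4. In the first pair the data cannot show whether spirit was used. In the second they cannot show whether the tie was clean.

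**What does the correction do?** Moving the answer leaves three tie answers and seven substance answers, 3 × 7 = 21 single-answer pairs. Clean thread with spirit is now one of them, even before open answers or multiple responses are allowed.

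**The case against.** Several points on the other side stand.

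- Section D does not forbid circling two answers. An interviewer who circles both clean thread and spirit loses nothing. If spirit alone is circled at the tie question, the spirit use is still in the data and only the tie material is lost. The form therefore does not fail for every spirit user. It leaves the result to the interviewer.
- The protocol has steps that might catch the slip. Interviews with birth attendants and elderly caregivers come first and can feed into the questionnaire (section 4.3.4). The questionnaire is pre-tested twice (sections 4.3.6 and 4.3.8), and the trial questionnaires are pre-tested again (section 4.4.10). These steps may correct the item, but nothing in the protocol does so.
- No scoring rule for cord care is given, and one may properly sit in an analysis plan that is not shown. A rule using only the cutting question would be untouched. Annex 15 lists cutting and care separately, which makes that reading less likely but does not exclude it.
- Cord care is one of four practices within one of four primary outcomes. The sample size rests on institutional delivery (section 4.4.8), which is unaffected.

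Three stronger readings are tempting and not supported.

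- **A bias between arms.** A reader might reason that spirit is commoner in facility births, which the intervention aims to increase. Assuming spirit in 30% to 80% of facility births and 5% of home births, the planned 23.5% and 33.5% delivery rates give 0.10 × (0.30 − 0.05) = 2.5 points to 0.10 × (0.80 − 0.05) = 7.5 points. But that is the difference in spirit use itself, which is a change in cord practice and not an error. It becomes a miscoding difference only if every spirit user is miscoded in the same direction, and the assumed rates have no source in the protocol.
- **A count of wrong records.** An assumed 5% to 30% spirit use gives 41 to 247 of the 823 women in sub-study two and 43 to 260 of the 868 per arm. These would be women exposed to the ambiguity, not women shown to be misclassified.
- **Damage to the 42% prevalence in section 4.3.5.** That value is a planning input from a cited survey, and Annex 6 cannot alter it.

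**Conclusion.** The point holds as a defect of the form. If one answer is taken per question, clean thread with spirit has no correct record, and either the tie material or the spirit use is lost. This can misclassify the trial's cord-care outcome and the local cord-care estimate in sub-study two.

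Size and direction cannot be stated, because the protocol gives neither a rate of spirit use nor a scoring rule. The conclusion rests on two assumptions: that one answer is taken per question, which the missing multiple-response instruction supports but does not prove, and that cord care is scored at least partly from the tie or substance question. It is a modest point about one component of a primary outcome and does not touch the basis of the sample size. It is still worth acting on, because the lost information cannot be fully recovered at analysis.

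**What to change.** Before pre-testing, make three edits to Annex 6 section D:

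1. Move spirit/alcohol from the tie question to the substance question as a category of its own.
2. Mark the substance question so that all applicable answers are circled, with the nothing answer used only alone.
3. Add an open answer with space to specify to both questions.

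How the cord-care variable is then scored can be left to the analysis plan, since the form will hold the facts it needs. The cost is a few lines on a questionnaire that is due for pre-testing anyway, with no extra visits, staff or participants. The edits concern how answers are coded and imply nothing about which cord treatment is right.

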**E. Warmth**

1. At what stage after delivery was the newborn dried up

1. Immediately before the placenta was delivered
2. Immediately after delivery of the placenta
3. After the mother was cleaned and wrapped
4. After the whole process of the delivery was completed
5. Not dried, just wrapped

2 .At what stage was the newborn wrapped up in a warm cloth

1. Immediately before the placenta was delivered
2. Immediately after the placenta was delivered
3. Long after the delivery was competed

3. What was the timing of the first bath after delivery?

1. Immediately after delivery;
2. Not immediately but within 6 hours;
3. 7-23 hours after;
4. Second day after delivery or later

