## 4.4.1 Introduction

The ultimate intervention will be based on data obtained from the two formative surveys and; based on our own knowledge about the context of Masindi and Kiryandongo and the subject of maternal and newborn care. The first study with health workers will inform the design of re-orienting health services at the antenatal clinic, while the community survey will form a basis for the appropriate educational messages to be delivered at the ANC clinics.

Primary outcomes of interest in this study are timely return ANC visits, completed four ANC visits, institutional delivery, and neonatal homecare practices. Secondary outcomes are post intervention community and health workers perceptions about the educational intervention offered by CHWs at the primary care facility.

The educational intervention will consist of **i)** a promotional team of community health workers supervised by a health assistant providing educational interventions at the primary care facility and; **ii)** the promotional team at the health centre using mobile phone reminders through Community Health Workers to pregnant women at the households.

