### 4.4.7 Study variables

## Independent/factor:

(i) Routine ANC care available in the health facilities (standard care);

(ii) *Promotional team* giving additional education care to pregnant women with periodic mobile phone reminders.

*Dependent/outcome variables*

1. Timely return ANC visits (return within seven days of the scheduled appointment date)
2. Completion of the four recommended ANC visits
3. Institutional deliveries
4. Newborn care practices:
5. Provision of warmth to the newborn
6. Initiation of breastfeeding within one hour of birth
7. Care for the cord
8. Immunization for the newborn-Polio 0 & 1; BCG within the neonatal period

We will, at the end of the study, assess perceptions of individual women who have participated in this intervention towards the integrated package by administering the tool described by Howie and others ([Howie J, Heaney D et al. 1998](#_ENREF_42)) elaborated in annex 15 (the Patient-Enablement Initiative (PEI).

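### Annex 6 codes the first bath partly in hours and partly by day, and has no code for a baby never wrapped, so these two warmth items cannot be recorded reliably

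*Protocol*

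**What the plan says.** Protocol, Annex 6, section E has three warmth items: drying, wrapping and first bath.

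- **First bath.** The codes are, in order: immediate; later but within 6 hours; "7-23 hours after"; and "Second day after delivery or later".
- **Wrapping.** Two codes place wrapping before or after delivery of the placenta. The third is "Long after the delivery was competed". There is no code for a baby never wrapped, and none for an unknown answer.
- **Drying.** This item does have a code for a baby who was not dried.

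Annex 6 is headed as the "data collection guide for Structured Interview for lactating women sub study two", and section 4.3.7 lists warmth among that survey's variables. For the trial, section 4.4.1 states: "Primary outcomes of interest in this study are timely return ANC visits, completed four ANC visits, institutional delivery, and neonatal homecare practices". Section 4.4.7 lists "Provision of warmth to the newborn" as a component of newborn care. Annex 15, part i, brings Annex 6 into the trial: "Assess for the different practices outlined annex 6 will be used to assess the following outcomes". The list that follows does not name warmth, wrapping or bathing. The same procedure gives the counselling content on bathing in hours: "Discuss bathing of the new baby how soon and how to delay (delay up to 24 hours".

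**The concern.** Response codes should be mutually exclusive and should cover every answer a mother can give. The bath codes change units between the third and the fourth, and the form has no rule for choosing when an overnight interval satisfies both. The change falls next to the 24-hour point that the counselling mentions. The wrapping item cannot record that wrapping did not happen, so such a baby is either given a timing code or left blank.

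Two uses are at stake. One is the sub-study two survey of 823 mothers, whose estimates of home practice are meant to shape the trial's messages. The other is the warmth component of the trial's newborn outcome, if it is taken from the same items. Error shared by both arms does not by itself favour one of them, but it biases a prevalence estimate and will usually dilute a contrast between arms. No sample size or power figure depends on these items.

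**Working it through.** The protocol gives no figure to reproduce. The check is a reading of the codes, followed by an illustration of how large the bath overlap could be.

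**1. Overlap.** Take a baby born at 20:00 and bathed at 08:00. Elapsed time is 12 hours, so the third bath code applies. The bath is on the next calendar day, so the fourth applies as well if it is read by the calendar.

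**2. Gaps.** Read literally, a bath between 6 and 7 hours fits no code, and one between 23 and 24 hours fits no hour code. A baby not yet bathed has no code either, although section A of Annex 6 admits babies in their first week.

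**3. Comparison within Annex 6.** Ages at death (section A) and timing of the first postnatal visit (section G) are coded in elapsed time, with cuts at 24 and 72 hours. Items on cord substances, resuscitation and weighing have a code for nothing or not done. The bath and wrapping items depart from the form's own practice.

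**4. Size of the overlap on the calendar reading.** Assume birth times are spread evenly over 24 hours. A bath t hours after birth (t below 24) falls on the next calendar day with probability t/24:

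| t (hours) | t/24 |
| --- | --- |
| 7 | 29% |
| 12 | 50% |
| 23 | 96% |

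If delays are also spread evenly from 7 to 23 hours, the mean is ((7 + 23)/2)/24 = 15/24 = 62.5%. A simulation gave 62.5%. Limiting baths to clock times from 07:00 to 19:00 changes nothing. Delays of 19 to 23 hours (4/16 of the range) always cross midnight and delays of 7 to 19 hours (12/16) cross it half the time: 4/16 × 1 + 12/16 × 0.5 = 62.5%.

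**5. Size on the other reading.** If the last code means 24 hours or more, the overlap is 0%. Only the narrow gaps in step 2 remain.

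**6. A 6-hour cut.** Confusion between the third and fourth codes does not matter here, because both lie above 6 hours. The calendar reading could in principle capture a bath within 6 hours that crosses midnight (6/24 = 25% at exactly 6 hours). If baths are given at 07:00 or later, however, a birth before midnight is always followed by a delay of more than 7 hours, so that overlap disappears.

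**7. Wrapping.** The documents do not say how often a baby is never wrapped, so this gap cannot be sized.

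**The case against.** The strongest reply is that the bath codes are ordered. Coming straight after a band ending at 23 hours, the last code is naturally read as 24 hours or more, and one line of interviewer training would settle it. This stands as a reason to treat the point as small. It does not remove it, because the form does not state that reading and section 4.4.9 has the trial questions put orally in another language by research assistants.

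The second reply is that the link to the trial is inferred. Annex 6 is labelled for sub-study two, the Annex 15 list omits warmth, and section 4.4.9 describes the trial tool only as semi-structured questionnaires. That is correct. The list also omits immunisation, which section 4.4.7 names as an outcome, so it is not exhaustive, and no other form shown measures warmth. The link is plausible but not stated. Sub-study two is affected whichever way it is resolved.

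Third, pre-tests are planned in sections 4.3.8 and 4.4.10 and may catch such faults. They are the natural occasion for the repair.

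A reader might go further and infer that the warmth component cannot be scored at all. The documents do not support that: the drying item is usable, a stated reading rescues most bath answers, and a never-wrapped baby can be left blank or written in. Nor do they support the inference that good thermal care is overstated. No section sets 24 hours as the cut for adequate warmth; the 24 hours in Annex 15 is counselling content.

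**Conclusion.** The point holds and is minor. As printed, section E cannot reliably record bath timing around 24 hours, and it cannot record that a baby was never wrapped. This applies directly to sub-study two, and to the trial's warmth component in so far as Annex 6 is reused for it.

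The size is unknown. Among babies bathed at 7 to 23 hours, the share fitting two codes runs from 0% (last code read as 24 hours or more) to about 62% on average (calendar reading, with birth times and delays spread evenly, both assumptions). A reader might turn this into an overstatement of delayed bathing. If 10% to 30% of all babies were bathed in that band, the result would be 0.10 × 0.625 = 6 to 0.30 × 0.625 = 19 percentage points. Those shares are not in the documents, and the result also needs every overlapping baby to be given the last code. It is a ceiling with a floor of zero, not an estimate.

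**What to change.** Before pre-testing, reword two items in section E of Annex 6.

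- **First bath**, in elapsed time only: immediately; later but within 6 hours; more than 6 but less than 24 hours; 24 hours or more; not yet bathed; don't know. These bands only make the record unambiguous; they do not set which timing counts as adequate.
- **Wrapping**: add not wrapped and don't know.
- Use the same codes in sub-study two and in the trial, and say in Annex 15, part i, that the warmth items are among those taken from Annex 6.

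The cost is the rewording of two items and one added line in the procedure. It needs no extra participants or visits. It should precede data collection, because an ambiguous bath answer cannot be resolved afterwards unless the times of birth and bath were noted.
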